### Primary outcomes in cross-over study

#### Spontaneous brain activity in resting state

After the exercise protocol and before the cognitive tasks, spontaneous brain activity will be measured with EEG while children rest in a seated position, in order to measure the peak frequency [43] and reactivity of the alpha wave [104, 105]. The dynamics of the alpha peak frequency (between 7 and 13 Hz) during a 3 min period will be calculated by means of a Hilbert transform [106]. Then, an average value and trend of the alpha peak frequency will be calculated. It has been postulated that the higher the alpha peak frequency, the greater general cognitive capacity and processing speed are [44]. We focus on alpha waves because this brainwave has traditionally associated with different theories of attention and conscious perception [107, 108]. The frequency of the alpha wave has been discovered to increase after a session of cognitive tasks [109–111]. Additionally, the power and frequency of alpha brainwaves prior to cognitive evaluation have been correlated to performance [112]. If PA exerts a positive effect over cognitive performance, a single session of PA should also cause an increase in alpha peak frequency. In fact, this was found by Gutmann et al. in two consecutive studies [43, 44]. However, a statistical relation between PA-induced increments in alpha peak frequency and cognitive performance is missing.

#### Working memory performance

Hits, misses, omissions, and accuracy will be calculated for targets and non-targets of the n-back task, as well as response latency.

#### Reading task

Seven questions with varying degree of comprehension complexity will be given after the texts are read. For every question there will be four alternatives to choose as the correct answer.

#### Cognitive load

We group several measures on this category because all of them have been related with the concept of cognitive load. The first two come from the EEG, and the other two from the eye-tracker.

##### P300

The P300 event-related potential associated with the different type of stimulus in the n-back (target and non-target) will be quantified according to amplitude and latency of the peak.

##### N400

This linguistics-related event-related potential also will be described according to latency and amplitude. Because it will be synchronized with the eye fixation on words during the reading task, it is conceptually a type of fixation-related potential.

##### Rapid pupil size variations

Pupil reacts to cognitive requirements and it has been associated with increases in cognitive load during various tasks including working memory and reading [113, 114]. The amount of high frequency variations in pupil diameter is estimated by a novel Index of Cognitive Activity [114], which increases with cognitive load. This measure can be represented as a continuous variable in time thanks to the high sampling rate of the eye-tracker. The Index of Cognitive Activity will be measured during the n-back and reading tasks.

##### Word fixation times

The length of visual fixations also has been associated with the processing time that the brain dedicates to elaborate a cognitive interpretation of perception. Average and standard deviation of fixations around words will be calculated for the reading task.

### Data analysis plan

#### Cross-sectional study

Descriptive data from participants will be summarized separately for boys and girls, and presented as means and standard deviations for continuous variables and as percentages for categorical variables. T-test or chi-square analysis will be used to establish sex differences where appropriate. Also, interaction analysis by sex will be performed previous to the main analysis.

Given that the first aim of the project is to associate PA, sedentarism, and physical fitness with brain structure and function, cognitive performance and academic achievement; general linear models will be employed. Additionally, multilevel random-effects models will be used. Furthermore, as knowledge about this relationship in Chilean population is scarce, mediation analyses will be performed with other relevant variables related to school context. The significance threshold for all analyses will be *p* < 0.05.

#### Cross-over study

Differences among condition will be calculated using general lineal models (95% confidence) and estimating the Hedges effect size [115]. Strength of effect will be assessed according to the following interpretation: trivial (0–0.19), small (0.20–0.49), medium (0.50–0.79) and large (0.80 and greater) [116]. The significance threshold analyses will be *p* < 0.05.Regarding missing data, it is anticipated that missing data could be due to faults in the EEG and eye-tracker, and thus will be missing at random. For this reason, multiple imputation will be used to address this issue.

In addition to performance in the task of working memory and reading, several neurocognitive variables (amplitude and latency of both potentials, frequency of the alpha wave, and variation of its amplitude with the opening of the eyes) will be studied statistically using a model of mixed effects, which initially will use the factors: subject, exercise protocol and cognitive ability (high or low performer). Subsequently, it will be extended to other factors (the rest of the measures of the Cogni-Action Project, such as body composition, sexual development status, anthropometric measures, socioeconomic, brain structure, etc.), to establish which factors and interaction between them have greater statistical significance in the acute effects of PA on cognitive and academic performance.

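### The cross-over calls some 17 to 24 overlapping measures primary, ranks none and tests them at p < 0.05 with no error control, although its 32 participants were sized on one 2-back measure

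*Protocol article*

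**What the plan says.** The heading "Primary outcomes in cross-over study" covers every subsection up to the data analysis plan:

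- **Resting EEG.** The recording is made "in order to measure the peak frequency [43] and reactivity of the alpha wave". "Then, an average value and trend of the alpha peak frequency will be calculated".
- **Working memory.** "Hits, misses, omissions, and accuracy will be calculated for targets and non-targets of the n-back task, as well as response latency".
- **Reading.** Seven multiple-choice comprehension questions.
- **Cognitive load.** "We group several measures on this category because all of them have been related with the concept of cognitive load". The group holds P300 amplitude and latency by stimulus type, N400 amplitude and latency, the pupil index in two tasks, and the mean and standard deviation of word fixations.

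No measure and no contrast between conditions is put first. In *Data analysis plan, Cross-over study*, conditions are compared with general linear models, and "The significance threshold analyses will be" p < 0.05. Mixed models follow. They are later extended to the project's other measures "to establish which factors and interaction between them have greater statistical significance in the acute effects of PA". The cross-sectional part has its own sentence: "The significance threshold for all analyses will be" p < 0.05.

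*Total sample size and power* for the cross-over derives the 32 from one 2-back variable: a difference of 71.50 ms with SDs of 93.1 and 91.6, power above 80%, alpha below 0.05 and 20% loss.

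**The concern.** The sample size gives one test a 5% chance of a false positive. The outcome section then gives primary standing to some two dozen measures, each read at that same 5%. Nothing in the article says which of them answers the trial's question. A chance result on any one could be reported as a significant primary effect, and the overall error rate would be far above the 5% a reader would assume. The later search, which orders factors and interactions by statistical significance in 32 boys, adds more chances of the same kind and carries no exploratory label. The Discussion hopes the results will inform ministerial and school programmes, so a chance finding could have consequences.

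A statistical analysis plan that is not shown could add a hierarchy. The point rests on what the article itself states, namely the primary label and the threshold, and not on an omission.

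**Working it through.** **1. The plan's own figure.** Pooled SD = √((93.1² + 91.6²)/2) = 92.35 ms. For two independent groups, two-sided 0.05 and 80% power:

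n per group = 2 × [92.35 × (1.960 + 0.842) / 71.5]² = 26.19

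26.19 × 1.2 = 31.4, which rounds up to 32. Rounding to 27 before adding losses gives 33 (× 1.2) or 34 (÷ 0.8). A one-sided test gives 21, or 26 to 27 with losses, and does not match. Sidedness is not stated. The 32 therefore fits one unadjusted two-sided test of one variable.

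**2. Counting the primary measures.**

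| Group | Count |
|---|---|
| Alpha: mean, trend, reactivity | 3 |
| n-back: 4 scores × 2 stimulus types, plus latency × 2 | 10 |
| Reading score (assumed one total) | 1 |
| P300: amplitude, latency × 2 stimulus types | 4 |
| N400: amplitude, latency | 2 |
| Pupil index × 2 tasks | 2 |
| Fixation mean and SD | 2 |
| **Total** | **24** |

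Counting latency once gives 23. Hits, misses and omissions largely mirror accuracy. Dropping those three for both stimulus types removes 6 more, leaving 17.

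**3. Independent measures, one test each, no true effect.** P(at least one p < 0.05) = 1 − 0.95^k:

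- k = 17: 0.58
- k = 23: 0.69
- k = 24: 0.71

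The probability passes one half at k = 14 (0.51).

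**4. Correlated measures.** The article gives no correlations, so these are assumed. A null three-condition cross-over was simulated with the 24 measures in the seven groups above, n = 26 and n = 32, and 3,000 runs per setting. Ranges are over the two values of n.

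| Correlation within / between groups | One condition test per measure | Any of three unadjusted pairs |
|---|---|---|
| 0 / 0 | 0.69–0.72 | 0.96 |
| 0.3 / 0.1 | 0.66–0.68 | 0.94–0.95 |
| 0.5 / 0.1 | 0.62–0.63 | 0.91–0.92 |
| 0.5 / 0.3 | 0.58–0.59 | 0.87 |
| 0.7 / 0.2 | 0.53–0.57 | 0.85–0.86 |
| 0.7 / 0.5 | 0.43–0.44 | 0.74–0.75 |
| 0.9 / 0.3 | 0.42 | 0.73 |
| 0.9 / 0 | 0.45–0.47 | 0.77–0.79 |

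The zero-correlation row brackets the exact 0.71. A single measure with three unadjusted pairs already gives 0.12.

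**5. Why not adjust across everything.** Bonferroni over 24 tests means 0.05/24 = 0.0021 per test. On the plan's own formula, n per group before losses rises from 27 to 52. Designating a primary is much cheaper.

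**The case against.** Several parts of the opposing case stand.

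- **The count depends on the rule used.** The n-back scores overlap, and latency by stimulus type is an inference. The mixed-model paragraph names a shorter list. Taking working memory as accuracy and latency, that list has about nine measures, and 1 − 0.95^9 = 0.37 if independent. It does not withdraw the primary label from the rest, and 0.37 is still well above 0.05.
- **Pairwise contrasts are not specified.** The plan speaks only of differences among conditions, which fits one test per measure. A reader might multiply 24 measures by three pairs and quote 1 − 0.95^72, about 98%. That figure treats the three pairs as independent, but the third difference is fixed by the other two. The simulated values apply instead, and only if pairs are compared unadjusted.
- **Imaging.** A reader might infer from the cross-sectional threshold that brain images will be tested voxel by voxel at an uncorrected 0.05. No section describes such a test. The threshold is compatible with corrected p-values, and that detail is commonly left to a fuller plan.
- **The aim is neuroelectric.** The Abstract and the end of the Background put neuroelectric activity at the centre. Imposing 2-back latency as the only primary outcome would put the sizing variable in place of the research question.
- **p-values are not the only output.** Hedges effect sizes and 95% confidence are also planned.

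None of this supplies a ranking or an error rule for the measures labelled primary.

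**Conclusion.** The concern holds for the cross-over. About 17 to 24 overlapping measures are primary, none leads, and all are read at p < 0.05 in a study sized for one test. With no true effect, the chance of at least one significant primary result is about 0.6 to 0.7 if the measures are independent. It is about 0.4 to 0.7 under the assumed correlations with one condition test each, and about 0.7 to 0.96 in the simulations if all pairs are also compared unadjusted. The lowest simulated value, 0.42, is more than eight times the nominal 0.05.

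These figures rest on the counting rule, one total reading score, and correlations that the article does not give. That the sized 2-back variable is response latency is inferred from its unit.

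A reader might go further and conclude that no result could be read as the trial's answer. The article does not support that: effect sizes are planned as well, and naming a primary outcome before analysis resolves the ambiguity.

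**What to change.** 1. Designate one primary outcome, or one small primary family that fits the neuroelectric and working-memory aim. 2-back response latency is a natural candidate because the sample size appears to rest on it, but the choice belongs to the investigators.
2. For each primary outcome, test condition overall first, then the pairwise contrasts with Holm. If the family has more than one member, apply Holm across it too.
3. Make the remaining measures secondary, with false-discovery control within each family (for example resting EEG, n-back, reading, event-related potentials, eye measures).
4. Report the extended search over factors and interactions as exploratory, without significance claims.

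This is a change of wording and needs no new data. The cost is stricter p-values for the adjusted measures: with Holm over three contrasts, the smallest p must fall below 0.05/3 = 0.017. If several primaries are kept, the stated power above 80% applies only to the unadjusted 2-back test, and the article should say so.

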**Fig. 1 Fig1:**
[figure not shown]
Cross-sectional and cross-over RCT study design

During the first part (i.e., cross-sectional study), measurements will take place in public and private schools, with two visits of 4 h each separated by 8 days. At the first visit, questionnaires, cognitive performance and anthropometric measurements will be assessed, followed by accelerometers placement. During the second visit, physical fitness and other questionnaires will be evaluated, plus accelerometer removal. A detailed description of all evaluations can be found in the measurements section.

Regarding the second part (i.e., crossover-randomized trial), children will be randomized to each protocol session, participating in all of them with two-weeks apart. Thus, they will assist to our gym to perform one of the three protocol and subsequently they will be move to a laboratory where they will undergo EEG and eye-tracking measurements during resting state condition and during two different cognitive tasks. More details can be found in following sections.

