### Design of cross-over acute trial

The design of the second part of the project will consist of a cross-over trial where the participants will perform, on different days, three different PA protocols with equal energy expenditure fashion in a random order. Before starting this part, schoolchildren will be evaluated by a physician (preparticipation physical evaluation), under previous authorization of their parents. The examination will consist in the realization of a complete clinical history and a general physical examination, with the purpose of verifying their health status and avoiding possible injuries or illnesses during PA protocols. Any adverse events occurring during the trial will be documented and submitted to the physician, which will analyze the exclusion of the participant from the trial.

Each child will visit our laboratory three times, every 2 weeks to ensure a “wash-out” period with the purpose of mitigating the PA effect from each protocol. The order will be determined using a computer-generated ordering system. The random sequence was generated by the web-based Research Randomizer (randomizer.org). A staff member responsible for recruitment will perform randomization. Participants will assist to the three different sessions at the same weekday (e.g., Monday) and at the same daytime to avoid differences in preceding school activities or circadian rhythms [82]. Participants will undergo a “Sedentary condition” (SC), sitting and watching a documentary on TV as has been used previously [82], and two different PA protocols consisting in “Moderate-Intensity Continuous Training” (MICT), continuous outdoor brisk walking/running; and “Cooperative High-Intensity Interval Training” (C-HIIT), composed of a circuit training with a partner (physical education teacher) (Fig. 1). These three protocols have been chosen in view of what corresponds to types of activities usually performed in schools. Thus, SC mimics the time spent during any academic lesson (i.e. mathematics or language lessons); MICT represents the typical activity in a PE class; and C-HIIT has been selected since it is postulated as an exercise protocol that could possibly be implemented in thethe PE class [92]. The three protocols are designed so that energy expenditure is equivalent between them, to eliminate differences in the energy expenditure as a possible confounding factor. Thus, the duration will be different among protocols.

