#### Reading task

Language processing will be assessed by a reading comprehension task where short paragraphs will be presented to be read normally. The eye-tracking technique will be employed to record eye position, movement and pupil diameter, simultaneous to the EEG record. Participants will seat in front of a monitor, at approximately 60 cm, placing their chin on an ergonomic stand piece, which helps to decrease head movements and improves eye-tracker signal precision. The reading task will be presented with the latest version of Tobii Pro Lab. After calibrating the system, each child is given a brief contextualization of the topic, before they start to read, knowing that later they will be asked seven comprehension questions with varying degrees of complexity. The participants must indicate the correct answer among four alternatives. It should be noted that three literary texts will be used, presented in a random fashion (1 per exercise condition). These texts will have the same difficulty, the same distribution of areas of interest, similar amount of words, and will be previously validated by a panel of experts. The reading of each word is expected to generate an EEG negative potential with latency close to 400 ms (N400). The amplitude, topographic distribution and latency of this potential are electrophysiological neuromarkers of linguistic ability in general, and the ability to construct meaning from words [103]. The eye-tracker will be used to study the ocular trajectory during reading and establish the moments when words are read. EEG and eye-tracking will be registered simultaneously to record eye movements related to reading, giving measures such as reading speed, fixation durations, number of fixations, among others), and to measure eye fixation related EEG potentials associated with cognitive load while reading words [50]. The reader should note that this potential coincides experimentally with the N400, so they may represent different brain processes superimposed, or be essentially the reflection of the same mechanism.

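### The stated crossover model has no period term, although the n-back is repeated at three sessions and no balancing of the orders is described: a moderate loss of precision, cheaply avoided

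*Protocol article*

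**What the plan says.** Under Design and participants, "children will be randomized to each protocol session, participating in all of them with two-weeks apart". Design of cross-over acute trial adds "Each child will visit our laboratory three times, every 2 weeks", with the interval justified as a wash-out, and keeps weekday and time of day the same for each boy.

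On allocation, the same section says "The order will be determined using a computer-generated ordering system. The random sequence was generated by the web-based Research Randomizer (randomizer.org". It mentions no blocks, Latin square or equal use of the six possible orders.

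The end of the C-HIIT subsection places the EEG, eye-tracking and cognitive tasks after each condition. No measurement before the condition on the same day is described. The n-back has no alternate form. For reading, "three literary texts will be used, presented in a random fashion (1 per exercise condition", and the texts are to be matched on difficulty, areas of interest and approximate length, and validated by experts.

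On analysis, the Cross-over study part of the Data analysis plan says "Differences among condition will be calculated using general lineal models (95% confidence". It then gives a mixed model "which initially will use the factors: subject, exercise protocol and cognitive ability (high or low performer". The later extension names only participant measures, such as body composition, maturity and socioeconomic status. Neither model includes period, sequence or text.

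**The concern.** A three-period crossover compares conditions within a boy, so whatever changes systematically from the first to the third session is mixed with those comparisons. Practice on a repeated working-memory task is the obvious candidate. The two-week interval deals with carryover of the exercise effect, not with learning, and there is no same-day baseline to absorb a session effect.

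If period is left out, practice acts in two ways. If the orders come out uneven, one condition falls later on average and its contrast shifts. Even with equal orders, the session-to-session change stays in the residual and widens every interval. Neither can be separated from condition in the model as written. The article names the model's factors itself, so this is more than a detail left to a fuller document.

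**Working it through.** **Inputs from the article** (Cross-over study, Total sample size and power): SDs 93.1 and 91.6 ms; planned difference 71.50 ms; 20% loss; 32 boys; α 0.05 (two-sided assumed); power above 80%.

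**The plan's own figure.** Pooled SD = √((93.1² + 91.6²)/2) = 92.35 ms. For two independent samples at 80% power, n = 2 × (1.96 + 0.8416)² × 92.35² / 71.5² = 26.19 per group, and 26.19 × 1.2 = 31.4, so 32. The stated size reproduces as a per-group number used as the crossover total. Nothing below changes it.

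**Assumptions, because the article is silent.** 26 completers (32 × 0.8 = 25.6); 92.35 ms taken as the SD of the within-boy difference between two conditions; practice equal for all boys and linear, at 0, 10, 30 or 60 ms per session; orders drawn by simple randomisation; 54 ms as an example of a smaller contrast.

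**Standard error without period.** Over the six orders, the session gap between two given conditions is ±1 in four and ±2 in two, so its mean square is (4 × 1 + 2 × 4)/6 = 2. With practice p per session, SE = √((92.35² + 2p²)/26):
- p = 0: √(8528.5/26) = 18.1 ms
- p = 10: √(8728.5/26) = 18.3 ms
- p = 30: √(10328.5/26) = 19.9 ms
- p = 60: √(15728.5/26) = 24.6 ms

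With period in the model, the simulated SE is about 18.4 ms whatever the practice effect.

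**Power**, simulated with fixed subject and condition effects (3,000 trials per cell; separate runs differ by a point or two):

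| Practice per session | 71.5 ms: without / with period | 54 ms: without / with period |
|---|---|---|
| 0 ms | 97% / 97% | 82% / 81% |
| 10 ms | 97% / 97% | 82% / 81% |
| 30 ms | 94% / 97% | 76% / 82% |
| 60 ms | 81% / 97% | 56% / 80% |

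A hand check of the last row, using SE 24.5 and critical value 2.01: 71.5/24.5 − 2.01 = 0.91, giving 82%; 54/24.5 − 2.01 = 0.19, giving about 58%. Type I error stayed at about 5% with and without period.

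**Chance imbalance.** The mean session gap between two conditions has SD √(2/26) = 0.28, so one SD moves a contrast by 0.28 × 30 = 8 ms or 0.28 × 60 = 17 ms. About 5% of draws exceed 1.96 × 0.28 ≈ 0.54 sessions, that is 16 or 32 ms.

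**Balancing alone is not enough.** In a separate simulation (32 boys, near-equal orders, within-subject SD 65 ms, 100 ms total gain over the sessions, period omitted), the residual SD rose to about 83 ms and the type I error fell to about 2%. Power for a 40 ms difference was 60%, against 69% with period.

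**The case against.** The best counter-argument is that the practice effect is assumed. The only related figure in the article is the control-group change of +2.05 ms in the cited 2-back trial, which is essentially no gain. It is one comparison at an unstated interval, so it does not rule out practice over three sessions, but it gives no support for 30–60 ms. The 54 ms contrast is not in the article either; at the planned 71.5 ms, power stays at about 81% even in the most extreme case. Both points stand and limit the severity.

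It is also fair that an article condenses: orders may have been balanced without this being reported, and the factor list is called initial. That answers the allocation point in part. It does not supply a period term, since the extension lists only participant measures.

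Three stronger readings are tempting and not supported:
- *That the condition contrasts are biased or false positives inflated.* Order is randomised, so neither holds over repeated randomisations. The shift concerns the one sample drawn.
- *That task performance is analysed without regard to the pairing within boys.* The sentence on general linear models names no outcome, and the mixed-model sentence can be read as covering performance too. The wording is ambiguous.
- *That differences between texts distort the reading results.* The texts are to be matched and validated, and the article gives no figure for a remaining difference.

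**Conclusion.** The point holds at moderate severity. The model as listed omits period in a design where a session effect is plausible and nothing else absorbs it. The consequence is lower precision and chance imbalance, not invalid inference.

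The loss is negligible at 10 ms practice per session or less. At 30 ms it is about 3 points of power for the planned difference, and at 60 ms about 16 points. Contrasts smaller than planned lose more, and the comparison of the two exercise conditions may be one of them. All of this rests on the assumed practice effect, on 26 completers and on a difference SD of 92 ms. The point applies fully to the n-back. In reading the text changes, so only familiarity with the procedure is tied to session.

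**What to change.** Add session number (1, 2, 3, as a categorical fixed effect) to every crossover model, for performance as well as EEG and eye-tracking outcomes, with subject as a random effect. For reading-task outcomes, add text as a factor. State how the orders and the texts were allocated. If any boys are not yet randomised, allocate the six orders in balanced blocks; since the article says the sequence was already generated, this may no longer be possible, and the model change does not depend on it.

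The cost is 2 within-subject degrees of freedom (62 to 60 with 32 boys), or 4 with text (62 to 58), and about 1–2 points of power if there is no practice effect. The sample size and data collection do not change. The planned multiple imputation and the high/low ability factor are separate questions and can stay as they are for this purpose.

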##### Total sample size and power

For feasibility reasons, the school chosen for the development of exercise sessions is close to our laboratory. Sample size is estimated according to the mean difference of two independent samples from a randomized controlled trial were a working memory task (2-back) was tested [56]. Children control group achieved a positive variation (∆ = 2.05 ms; SD = 93.1) while exercise group a negative variation (∆ = − 69.45 ms; SD = 91.6) [56]. A loss rate of 20% was considered. Statistical power analysis indicated that at least 32 participants would yield adequate power (i.e., > 80%) and α (i.e., < 0.05), with a detectable variation of 71.50 ms (∆ between experimental conditions – control condition).

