
### Cognitive performance

#### NeuroCognitive performance test (NCPT)

The NCPT (Lumos Labs, Inc.) is used to assess cognitive performance [68]. It is a brief, repeatable, web-based platform of cognitive tasks intended to measure functioning across several cognitive domains including: working memory, visuospatial memory, psychomotor speed, fluid and logical reasoning, response inhibition, numerical calculation, and selective and divided attention. The NCPT has demonstrated adequate reliability and validity as a measure of cognitive performance, and in good concordance with pencil-paper assessments [68]. Eight cognitive tasks will be assessed in this study (Fig. 2): i) “Trail Making A” and ii) “Trail Making B” estimate attention, cognitive flexibility and processing speed, and are based on the Army Individual Test Battery [69] and the Halstead-Reitan Battery, respectively [70]; iii) “Forward Memory Span” and iv) “Reverse Memory Span” determine visual short-term and working memory, respectively, and are based on the Corsi Blocks tasks [71]; v) “Balance” based on Wechsler Intelligence for Children IV [72] and Piagetian Balance Beam Tasks [49], which judges for quantitative and analogical reasoning; vi) “Digit Symbol Coding”, based on the Digit Symbol Substitution Task [73] and evaluates processing speed; vii) “Go/No-Go” task that checks for response inhibition control and processing speed; and finally viii) “Progressive Matrices”, based on established matrix reasoning assessments [74] and is designed to assess problem solving and fluid reasoning.

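### The cross-over mixed model enters cognitive ability as a high/low split, which costs information on the ability effect that a continuous pre-session score would keep

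*Protocol article*

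**What the plan says.** The Data analysis plan (Cross-over study) describes a mixed-effects model for event-related potential amplitude and latency and for the alpha-wave measures, with three starting factors: the subject, the exercise protocol and "cognitive ability (high or low performer"). The same paragraph then extends the model to other measures of the project, in order "to establish which factors and interaction between them have greater statistical significance in the acute effects of PA on cognitive and academic performance". It does not say that ability will go back to a continuous scale at that stage. Interactions are mentioned only with this extension; the initial list has no protocol-by-ability term.

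The article does not say which score defines a high or low performer or where the line falls. Two sources are conceivable:

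- **NCPT.** In the cross-sectional part, "The NCPT (Lumos Labs, Inc.) is used to assess cognitive performance", through eight tasks covering attention, span, speed, reasoning and inhibition.
- **N-back task of the cross-over sessions.** The section Working memory performance, under the primary cross-over outcomes, says: "Hits, misses, omissions, and accuracy will be calculated for targets and non-targets of the n-back task, as well as response latency".

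The cross-over sample size section states that "at least 32 participants would yield adequate power (i.e., > 80%) and α (i.e., < 0.05), with a detectable variation of 71.50 ms", with a 20% loss rate taken into account.

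**The concern.** Splitting a graded trait treats all boys on one side of the line as alike and separates boys who sit just either side of it. Ability is one of three starting factors and, apart from subject, the only participant characteristic among them. The declared purpose of the extended modelling includes finding which factors modify the acute effect of exercise, and ability is the natural first candidate. With 32 boys at most, any such question has little power to begin with, so an avoidable loss matters. The two-level form is written into the article; it is a stated choice, not a detail left to another document.

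**Working it through.** **1. The plan's own figure.** The article gives no figure for the cost of the split. The only related figure is the sample size, reproduced here to fix the numbers used below.

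- Inputs, from the cross-over sample size section: "Children control group achieved a positive variation (∆ = 2.05 ms; SD = 93.1") and "exercise group a negative variation (∆ = − 69.45 ms; SD = 91.6").
- Difference: 2.05 + 69.45 = 71.50 ms. Pooled SD: √[(93.1² + 91.6²)/2] = 92.35 ms.
- Two-sided α of 0.05 and 80% power: 2 × [92.35 × (1.960 + 0.842)/71.50]² = 26.19.
- Allowing 20%: 26.19 × 1.2 = 31.4, rounded up to 32. Rounding to 27 first gives 33 (27 × 1.2) or 34 (27/0.8).

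The stated 32 is therefore reproduced. After 20% loss, 32 × 0.8 = 25.6, or about 26 boys. Ability does not enter this calculation.

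**2. Information kept by a two-level split.** Assume a normal score and a linear effect. For a cut that leaves a proportion p below it, at standard normal point c, the split keeps

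φ(c)² / [p(1 − p)]

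of the information on the slope. At the median, φ(0)² / 0.25 = (1/2π)/0.25 = 2/π = 0.637, a loss of 36.3%. Uneven cuts lose more:

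| Cut | Information lost |
|---|---|
| 50/50 | 36% |
| 60/40 | 38% |
| 67/33 | 41% |
| 75/25 | 46% |
| 80/20 | 51% |
| 90/10 | 66% |

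At the median cut, 32 × 0.637 = 20.4 and 26 × 0.637 = 16.6. So 32 boys tell as much about ability as about 20 would with the continuous score (32 × 0.363 = 11.6, about 12 boys lost), and 26 boys as much as about 17.

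**3. Other score shapes, cut at the median.** The loss is one minus the squared correlation between the score and its split, from one million simulated values per shape.

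| Shape | Information lost |
|---|---|
| Strongly bimodal | 19% |
| Uniform | 25% |
| t with 4 df | 50% |
| Exponential | 52% |

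**4. Power.** One within-boy contrast between two conditions was regressed on ability, either continuous or split at the sample median: normal data, two-sided α of 0.05, 20,000 simulated data sets per setting. The true correlation between ability and the contrast is an assumption; the article gives no value.

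| Assumed correlation | n = 32: continuous / split | n = 26: continuous / split |
|---|---|---|
| 0.3 | 39% / 26% | 32% / 22% |
| 0.4 | 64% / 43% | 54% / 36% |
| 0.5 | 85% / 64% | 76% / 54% |

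As a check, the split shrinks a correlation of 0.5 to 0.5 × √0.637 = 0.40. The split power at 0.5 (64% and 54%) matches the continuous power at 0.4.

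**The case against.** **The size is not in the document.** The article gives no score, distribution or cut. A reader might infer that the plan simply discards a third of its information. That does not follow: 36% needs a normal score, a linear effect and a median cut. This objection stands, so the figure is given as conditional and with its range.

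**The main question is untouched.** The aim of the second part is the acute effect of the conditions, compared within each boy. A reader might infer that this comparison loses information or that 32 is no longer enough. Neither is so: a trait fixed within the boy does not drive the within-boy contrast, and the sample size rests on a reaction-time difference alone. This stands in full.

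**The initial model names no interaction.** The power figures concern ability as a modifier of the exercise effect, which the article raises only for the extended model. This also stands. The proportional loss in step 2 applies equally to an ability main effect.

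**Circularity is not shown.** A reader might infer that high and low performers will be formed from the cross-over n-back, so that the factor is built from an outcome. Nothing in the article says so. It does not rule it out either, so the point serves only as a caution in the fix. The missing score and cut-point are details that an article may leave to the full plan and are not held against it.

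**The NCPT may not be ready to use.** No composite score is described, and the cross-over criteria do not require a valid NCPT. The planned extension to the project's other measures, and the listing of the cross-over criteria under Subsample, imply that the boys have their cross-sectional data, but the article does not state it. This limits how confidently the change can be called free.

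**Conclusion.** The point holds in a limited form. The article fixes ability as two levels, nothing elsewhere reverses this, and a continuous pre-session score is the better method. Under the three assumptions, the split loses about 36% of the information on the ability effect or on an ability-by-condition interaction. That is the smallest loss from any single cut of a normal score, and no shape tried lost less than about 19%. At an assumed correlation of 0.5, power falls by about 21 points with 32 boys (85% to 64%) and 22 points with 26 (76% to 54%). The consequence is confined to the exploratory question of how ability relates to the outcomes or to the response to exercise. Severity is minor.

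**What to change.** - Replace the high/low factor with a cognitive score obtained before the sessions: one named NCPT score, or a composite defined in advance, from the cross-sectional part. Enter it as a centred continuous covariate.
- Include its interaction with condition wherever effect modification is examined.
- State that boys will not be classified by their cross-over n-back or reading results, which are outcomes.
- Keep high and low groups for graphs and descriptive display only.

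The cost is mainly wording. One NCPT score or composite has to be chosen in advance, a linear relation is assumed (and can be checked graphically), and the score must be available for every cross-over boy, which should be confirmed. If two groups are kept, the score, the cut and the reason should be fixed before the data are seen.
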